### Sample size

At the time we were developing the study we could find no systematic reviews of lifestyle interventions in pregnant women, so we based our sample size on a systematic review of interventions with obese adults, which found a mean weight loss of 7.9 kg (8.5%) during the first 6 months of interventions involving diet and exercise, after which weight was gradually regained, by 48 months a mean weight loss of 3.9 kg (4%) was maintained [28]. Results for trials which included only obese women (mean BMI+/=30 at baseline) demonstrated weight loss of a similar magnitude at 12 months [28]. In order for an individually randomised trial to have 80% power to detect a moderate effect size of 0.333 for a difference in BMI at 12 month follow-up of 1.5 kg/m^2^ (SD = 4.5), at a 5% significance level, 143 women per group would be required. Little pertinent data are available for the estimation of the intra-cluster correlation coefficient (ICC). Assuming an ICC of 0.02, if 20 maternity units were recruited across England and Wales, a variance inflation factor of 1.4 would result, so the total sample size is therefore inflated to 400 to detect the difference stated above and we would require an average of 20 women per unit. This would allow for a variance inflation factor of 1.4 (ICC = 0.02) [73]. In trials investigating weight management interventions in pregnant women, losses to follow-up range considerably from 5% to 38% [58,59,74-76], therefore we have allowed for a drop out of 30% and intend to recruit 570 women.

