### Rationale

Pregnancy is a time of change in women’s lives and is a potentially important point at which to influence women’s health behaviours as well as those of other family members [56]. Weight loss interventions with one individual can have spin-off effects on other family members [57]. Therefore, intervening with pregnant women and equipping them with the skills, knowledge and support necessary to manage their weight effectively, both during their pregnancy as well as after (thereby preventing excessive weight gain during pregnancy and retention of weight), is an important step in tackling obesity in this group.

An effective intervention would decrease obesity-related health risks for the women, reduce the risk of complications for mother and baby during childbirth and reduce health service costs. This could have a long term impact on not only the mother, but the child and other family members, resulting in far reaching public health benefits [56,57]. Although trials targeting GWG or weight loss postpartum by using advice on diet and/or physical activity have had some success [58,59], many studies have methodological problems including issues with randomisation and blinding, poor retention, incomplete follow-up data, small sample sizes, issues relating to intervention fidelity, poor description of the intervention and lack of a theoretical basis [58,60]. As such, more evidence is required. This trial seeks to address some of these methodological shortcomings, in that: it is adequately powered; it is theory-based; moderators of intervention effect are being measured; there are a number of different strategies in place to retain participants; there is a detailed process evaluation assessing issues like fidelity; and, there is a cost effectiveness analysis. As far as we are aware no RCTs of pregnancy or postpartum interventions have included an assessment of cost effectiveness. This trial will test a theory-based intervention targeting longer term postpartum weight control as well as weight gain during pregnancy.

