### Analysis

#### Quantitative analysis

The main analysis will be by intention to treat and will compare the primary outcome of BMI at 12 months postpartum in the intervention and control groups. Multilevel modelling will be used to account for clustering within antenatal unit and individual effects. A two level linear regression model will include baseline BMI (measured at recruitment) as a covariate. Both levels will be considered ‘random effects’ i.e. patients and units are drawn randomly from a larger population of patients and units. Cluster level variables include those used to balance the randomisation: antenatal unit size; proportion of women with BMI +/=30, geographic location and ethnic mix.

For the BMI data, positively skew distributed form is anticipated and will be checked prior to analysis. Log transformation will be considered, not only to deal with the non-normality but to allow interpretation of differences between arms in percentage terms. To further aid clinical interpretation of the intervention effect, analysis of log transformed weight at 12 months postpartum will also be considered, with baseline log weight and log height as covariates. The results can then be expressed in terms of BMI or weight along with a 95% confidence interval. The intra-cluster correlation (ICC) for the primary outcome will be calculated and reported.

Intention to treat analysis will be used for all secondary outcomes. Analysis of secondary outcomes will also use multilevel modelling incorporating baseline scores as covariates where appropriate. Two level linear regression models will be used for outcomes such as pregnancy weight gain and waist-to hip ratio and validated questionnaire scores, while logistic models will be used for clinical event outcomes. 95% confidence intervals for the intervention effect will be calculated. The ICC for each secondary outcome will be calculated and reported.

The impact of individual demographic factors as well as theoretical mediators (self-efficacy, social support, intrinsic motivation and self-regulation) on the intervention effect using interaction terms included in the main analysis models will be examined. Individual demographic variables include age, ethnicity, smoking status, previous weight loss history, psychological wellbeing and social class. We also intend to carry out tests for mediator variables [97].

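### The sample size applies a design effect but makes no allowance for having only 20 units: on its own inputs an unadjusted comparison has about 76% power, not 80%

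*Protocol article*

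**What the plan says.** All statements are in the protocol article.

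- **Sample size, starting point.** The calculation begins from individual randomisation: "In order for an individually randomised trial to have 80% power to detect a moderate effect size of 0.333". The target is a "difference in BMI at 12 month follow-up of 1.5 kg/m^2^ (SD = 4.5" kg/m², and "at a 5% significance level, 143 women per group would be required".
- **Sample size, clustering step.** "Assuming an ICC of 0.02, if 20 maternity units were recruited across England and Wales, a variance inflation factor of 1.4 would result", and "the total sample size is therefore inflated to 400 to detect the difference stated above". This is described as an average of 20 women per unit. An allowance of 30% for drop-out brings recruitment to 570.
- **Abstract, Methods/design.** Units are split 10 to intervention and 10 to control.
- **Rationale.** Among the trial's advantages over earlier work the article lists that "it is adequately powered".
- **Quantitative analysis.** The primary outcome is analysed with units as random effects: "A two level linear regression model will include baseline BMI (measured at recruitment) as a covariate". It adds: "Cluster level variables include those used to balance the randomisation". The section does not name an estimation method or a degrees-of-freedom method.

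**The concern.** A design effect accounts for the extra variance that clustering brings. It does not account for having to estimate the between-unit variance from few units. With 10 units per arm, the test of the intervention effect rests on 20 − 2 = 18 degrees of freedom, so the critical value is 2.101 and not 1.960. Inflating an individually randomised sample size therefore overstates power when units are few.

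The section presents 400 as enough to detect the stated difference, which carries the 80% over to the cluster design. The section also gives no credit for the baseline-BMI covariate in the planned model and does not say whether the SD of 4.5 already reflects it. The implied 80% is thus not the power of the unadjusted cluster comparison, and it cannot be identified as the power of the planned analysis. This matters most if the result is null, when readers need to know what difference the trial could have detected.

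**Working it through.** **Inputs from the protocol:** difference 1.5 kg/m²; SD 4.5; ICC 0.02; 20 units, 10 per arm; 400 analysed, so 200 per arm and 20 per unit; 5% level. Sidedness is not stated. Two-sided reproduces the stated n.

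**1. The protocol's own figures**
- n per group, normal formula: 2 × (1.960 + 0.842)² × 4.5² / 1.5² = 141.3, so 142. The t-test version gives 142.2, rounded up to 143.
- Design effect: 1 + (20 − 1) × 0.02 = 1.38, stated as 1.4.
- Total: 2 × 143 × 1.4 = 400.4, stated as 400.
- Drop-out: 400 / 0.7 = 571.4, stated as 570.

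The chain reproduces to within rounding.

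**2. Power of the unadjusted cluster comparison**

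SE = SD × √(2 × DE / 200); noncentrality = 1.5 / SE.

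| Design effect | SE | Noncentrality | Power, normal reference | Power, t on 18 df |
|---|---|---|---|---|
| 1.38 | 4.5 × √0.0138 = 0.529 | 2.84 | 81.0% | 76.5% |
| 1.40 | 4.5 × √0.0140 = 0.532 | 2.82 | 80.4% | 75.9% |

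The implied 80% appears only with the large-sample reference. The same inputs on 18 df give about 76%.

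**3. Power of the planned baseline-adjusted analysis**

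This step needs two assumptions that the protocol does not settle: that the SD of 4.5 is unadjusted, and a value for the correlation r between baseline and 12-month BMI. I apply r equally within and between units, so the SD becomes 4.5 × √(1 − r²). Design effect 1.38, 18 df:

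| Assumed r | Adjusted SD | Power |
|---|---|---|
| 0 | 4.50 | 76.5% |
| 0.3 | 4.29 | about 80% |
| 0.5 | 3.90 | 87% |
| 0.7 | 3.21 | 96% |

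If the SD of 4.5 is already baseline-adjusted, none of this gain is available and about 76% is the figure for the planned analysis too.

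**4. Sensitivity to the degrees of freedom**

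If the four balancing variables were fitted at one parameter each (an assumption, since their coding is not given), 14 df remain. The unadjusted power is then 74.5 to 75.1%, with no credit for any between-unit variance that those variables remove. The correlation needed to regain 80% rises to about 0.34.

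**The case against.** The strongest reply is that nothing is miscalculated. The words about 80% power are attached to the individually randomised trial, for which 143 per group is right, and the design-effect step is a standard approximation. That stands as a description of the arithmetic. It does not rescue the conclusion, because the section goes on to say that 400 suffices for the same difference in the cluster trial.

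The second reply is that the planned analysis adjusts for baseline BMI, so an unadjusted calculation is probably conservative. This has real force. A correlation of about 0.3 is enough, and that would be low for the same woman's BMI computed from one height measurement. It limits the point to the calculation as written. It does not remove it, because the protocol gives no correlation and does not say what its SD represents.

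A reader might go further and infer that the primary model also treats the 20 units as unlimited, so that its confidence interval is too narrow and the 5% level is not kept. The document does not support this. Quantitative analysis specifies a two-level model with random unit effects and never states maximum likelihood, a normal reference or any other large-sample inference. The degrees-of-freedom method is detail commonly left to an analysis plan, which is not shown here. Inflation would follow only under choices that the document does not make. In simulation with 20 units of 20, ICC 0.02 and no unit-level covariates, a normal reference gives a type I error of about 5.8% with REML and 6.7% with ML. A t reference on 18 df gives 4.3% and 5.1%.

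Nor is the claim of adequate power in the Rationale shown to be false. It is unsupported by the calculation as written, and may well hold for the adjusted analysis.

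**Conclusion.** The point holds for the sample-size calculation. On the stated inputs, with two-sided 5% and equal units of 20, the unadjusted comparison of 10 with 10 units has 75.9 to 76.5% power, about 4 points below the implied 80%. The cause is the missing allowance for 18 between-unit degrees of freedom.

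The shortfall need not carry over to the planned analysis. If the SD of 4.5 is unadjusted, power is about 80% at r = 0.3, 87% at r = 0.5 and 96% at r = 0.7. These figures rest on an assumed r and on the stated ICC, for which the section itself says there is little relevant data. At an assumed ICC of 0.05 the unadjusted power on 18 df would be about 62%.

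No error in the primary model or in its type I error is established. Severity is minor to moderate: a stated design figure needs correcting, but the design, the recruitment target and the primary model need not change.

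**What to change.** In Sample size:

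1. Restate the power as about 76% for an unadjusted difference of 1.5 kg/m² with 20 units of 20 analysed women, ICC 0.02 and a t reference on 18 df.
2. Say whether the SD of 4.5 is before or after adjustment for baseline BMI.
3. Give the power of the planned baseline-adjusted analysis over a stated range of baseline/12-month correlations, for example 0.3 to 0.7, and rest the adequacy claim in the Rationale on that.

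As a suggestion for the analysis plan only, name the inference method for the two-level linear models, for example REML with Kenward-Roger or Satterthwaite degrees of freedom.

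The cost is a few sentences and a slightly less favourable unadjusted figure. No extra women or units are needed.

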### Centre recruitment

Twenty maternity units across England and Wales will be recruited, ensuring a spread of different demographic areas, e.g. areas of high minority populations and low socio-economic status. All units will use electronic maternity information systems, in order to facilitate collection of outcome data and will have at least 1500 births per year. We will exclude any centre currently running a service similar to the HELP intervention.

### Participant recruitment

570 pregnant women with a Body Mass Index (BMI) of +/=30 aged 18 years or older and between 12 and 20 weeks gestation will be recruited. Potentially eligible participants will be approached at their earliest antenatal appointment by NHS midwives or researchers, who will provide an information sheet and briefly describe the study. The decision to approach women will not be made by the midwife delivering the intervention. If women are eligible and interested in participating, they will be contacted by the research midwife (local Principal Investigator (PI)) to discuss the study in greater detail and arrange a baseline home visit where informed consent and baseline measures will be taken.

The approaching midwife/researcher will provide the women with a comprehensive information sheet prior to the baseline visit and adequate time will be given for them to read the material and to ask any questions they have about the study. Women will be reminded that they retain the right to withdraw consent for participation in any aspect of the trial at any time without their routinely available NHS care being affected. Midwives/researchers will be trained in Good Clinical Practice and all study procedures. The participant’s GP, named midwife and obstetrician, if applicable, will be informed that she is taking part in the study.

A screening form will be completed to record the number of women approached about the study, eligibility, and at what stage women declined to take part in the study (e.g. when first approached or at the consent stage).

### Exclusion criteria

Women will be excluded from being recruited into the study if they:

1) are unable to understand the intervention, e.g. have insufficient understanding of spoken English;

2) have any detected pregnancy related complications e.g. multiple pregnancy, foetal anomaly, current antenatal, maternal or foetal complications, recurrent miscarriage (three or more) or previous pre-eclampsia;

3) have any previous medical complications e.g. cardiac disease, serious respiratory disease including severe asthma, diabetes mellitus, serious mental illness/psychological illness, epilepsy requiring anticonvulsant therapy or hypertension requiring treatment;

4) have nutritional complications e.g. serious physical or psychological disorders (eating disorders) or previous surgery for weight problems;

5) are involved in any other research that may affect any of the outcome measures that are being investigated in this study.

This list is not considered exhaustive. If the midwife considers that the woman has other serious complications that would affect her suitability to participate in the study, the midwife may at her discretion exclude the woman from recruitment noting on the recruitment form the reason why the woman has been excluded. If medical or obstetric complications arise while a participant is involved in the study advice will be taken from the woman’s lead obstetrician on whether she should withdraw from the intervention. If a woman is withdrawn on clinical grounds the study team will still complete follow-up if the woman is willing.

### Site randomisation

Sites will be randomised when all necessary approvals are obtained. Randomisation will be completed to give optimal balance for geographic region, maternity unit size, ethnic mix and the proportion of the maternity unit pregnant patient population with a BMI +/=30 [77-81]. A process of optimal allocation will be undertaken [79-81]. This will involve calculation of all possible allocations and a balance statistic for each one. A proportion of all allocations with the greatest degree of balance will be identified and passed to the independent statistician on the Trial Steering Committee (TSC) blinded to unit. He will randomly select a single allocation. This will then be returned to the trial statistician. The process of optimal allocation will be carried out in two blocks of ten sites with each block allocation being chosen by the independent statistician from the 25% most optimal allocations in each case. A statistician independent of the study but within the South East Wales Trials Unit will create random numbers for intervention/control arm allocation. The rest of the trial team and the clinics themselves will be informed of allocation after site recruitment.

In the event of delayed approvals for the maternity units such that it is not possible to randomise the second block of 10 sites together, minimisation will be used. A random component will be added to the minimisation algorithm using an 80% weighted randomisation. The allocations of the first block will be used to balance the remaining sites [77,78].

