### Design

The study is a cluster randomised controlled trial; the maternity units, rather than individual participants, are the units of randomisation. This is to minimise risk of contamination of control participants through two potential mechanisms. Firstly, the use of aspects of the intervention with control participants by site midwives who have been trained in study procedures and secondly, the passage of information regarding the intervention between intervention and control participants who are acquainted and attend the same maternity unit.

In addition to receiving usual NHS care, all study participants will be provided with 2 study leaflets: 1) a Food Standards Association eating during pregnancy leaflet detailing foods which should be avoided during pregnancy and 2) an exercise during pregnancy leaflet detailing recommended physical activity during pregnancy and warning signs for when to stop exercise and seek medical attention. Participants attending intervention sites will also receive the HELP Study intervention which is described below. Participants attending control sites will only receive usual care and the leaflets.

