### Follow-up & drop out

Baseline data will be collected by local PIs. Follow-up data will be collected by local PIs or research staff in each centre, or network research staff. For units in Wales this will be the Clinical Studies Officers employed by National Institute for Social Care and Health Research Clinical Research Collaboration (NISCHR CRC), in England the research nurses employed by the Comprehensive Local Research Networks (CLRN). The follow-up visits will be completed in the participants’ home or at a location of the participants’ choice. The follow-up appointments are timed to occur at important milestones both pre and postnatally: 36 weeks gestation, 6 weeks postpartum, 6 months postpartum and 12 months postpartum.

Every effort will be made to reduce loss to follow-up: women will be visited at a convenient location of their choice for all follow-up appointments. In order to improve response rates, participants will be contacted to rearrange any missed follow-up appointments, participant-nominated contacts will be collected at baseline in order to facilitate contact at follow-up appointments, participants will be posted study updates in the form of newsletters and follow-up calendars, and each participant will be provided with a £10 high street voucher as a thank you for completing each follow-up. A HELP study website will be used to provide study updates (http://medicine.cf.ac.uk/help-study/), and a minimum dataset will be developed to collect follow-up data by telephone for those participants who are unwilling or unable to meet with the researcher.

In order to prevent resentful demoralisation in the control group, each of these women will be offered 12 weeks normal community-based Slimming World sessions free of charge after her 12 month follow-up is complete. Any woman who undergoes a miscarriage, stillbirth, neonatal death or termination of pregnancy will be given an open option whether or not they wish to continue participation in the study.

All site study staff including the Intervention Midwife and Slimming World consultant will be visited by the research team and updated via regular contact and newsletters in order to encourage continued enthusiasm. In addition, to prevent disappointment following randomisation in the control sites, if results from the study prove positive units allocated to the control group will then be offered training for their midwives in the intervention.

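### Unit staff can know the arm while they enrol women, and nothing in the plan withholds it from women until baseline is complete, so differential recruitment is possible and baseline BMI would not correct it

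*Protocol article*

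**What the plan says.** All references are to the protocol article.

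- Design: "the maternity units, rather than individual participants, are the units of randomisation".
- Site randomisation: "Sites will be randomised when all necessary approvals are obtained". On disclosure: "The rest of the trial team and the clinics themselves will be informed of allocation after site recruitment".
- Study intervention: the weekly groups are open to a woman from the moment she is recruited, at 12 to 20 weeks of gestation.
- Participant recruitment: "Potentially eligible participants will be approached at their earliest antenatal appointment by NHS midwives or researchers". An interested, eligible woman is then "contacted by the research midwife (local Principal Investigator (PI)) to discuss the study in greater detail and arrange a baseline home visit", and that visit covers both consent and baseline measurement. The intervention midwife does not decide whom to approach. A screening form records numbers approached, eligibility and the stage at which women decline.
- Exclusion criteria: the list is open-ended. A midwife may exclude a woman at her own discretion and notes the reason.
- Follow-up & drop out: "Baseline data will be collected by local PIs".
- Process evaluation, Table 3: recruitment is compared across sites, and potentially eligible women are compared with those recruited.
- Protecting against bias: unit staff are expected to favour the intervention. The section deals with disappointment at control units, differential dropout and the difficulty of blinding outcome collection. It does not discuss differential recruitment.
- Quantitative analysis: "A two level linear regression model will include baseline BMI (measured at recruitment) as a covariate". The cluster-level balancing variables are also named. Individual demographic factors appear only in interaction analyses.

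**The concern.** Randomising units makes the units comparable. It does not make the women comparable if they are selected, or select themselves, after the arm is known to someone who influences enrolment. There are two routes here. Staff who know the arm could approach, encourage or exclude differently. Women who learn the arm before consenting would be responding to different offers: weekly groups plus usual care, or usual care plus leaflets.

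If readiness to change then differs between arms and is related to 12-month BMI, the primary comparison mixes the intervention effect with a difference in who enrolled. Intention to treat keeps the enrolled groups intact, but they are not the groups that randomisation made comparable. Recruiting more women does not shrink a bias of this kind.

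**Working it through.** **Who can know the arm, and when.** Clinics are told after site recruitment. The natural reading is after units have been recruited. The other reading, after the women at a site have been recruited, does not fit groups that each woman may join on recruitment at 12 to 20 weeks. An intervention unit must therefore know its arm while it is still enrolling. Consent and baseline are taken by the local research midwife, with no statement that she is blinded or independent of the unit.

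**What the safeguards do.** Keeping the intervention midwife out of the approach decision separates roles but does not conceal the arm. The screening form, the exclusion reasons and the Table 3 comparisons show selection after it has happened. Table 3 promises dropout by trial arm, but for recruitment it promises comparison across sites, not by arm.

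**The plan's own figures.** These are not in dispute.

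- Per group, two-sided 5%, 80% power: 2 × (1.96 + 0.84)² × 4.5² / 1.5² gives 142 (stated 143).
- Variance inflation: 1 + (20 − 1) × 0.02 = 1.38 (stated 1.4). 286 × 1.4 = 400.4 (stated 400).
- Dropout: 400 / 0.70 = 571.4, or 572 rounded up (stated 570).

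**Illustrative size of the bias.** From the document: target 1.5 kg/m², SD 4.5. Assumed, because the document gives no figure:

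- difference between arms in motivation: 0.3 to 0.5 SD;
- partial correlation of motivation with 12-month BMI given baseline BMI: 0.2 to 0.3;
- correlation of baseline with 12-month BMI: 0.7.

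Residual SD = 4.5 × √(1 − 0.7²) = 3.21.

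Bias = imbalance × partial correlation × residual SD:

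- lower: 0.3 × 0.2 × 3.21 = 0.19 kg/m², and 0.19 / 1.5 = 13%;
- upper: 0.5 × 0.3 × 3.21 = 0.48 kg/m², and 0.48 / 1.5 = 32%.

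**Effect on the test.** With 200 analysed per arm and the same inflation of 1.38 applied to the residual, SE = 3.21 × √(2 × 1.38 / 200) = 0.38. If the intervention truly had no effect, the two-sided rejection rate would be Φ(−1.96 + bias/SE) + Φ(−1.96 − bias/SE). That is about 8% at a bias of 0.19 and about 25% at 0.48, against a nominal 5%. Adjusting for baseline BMI narrows the SE, so a given residual bias weighs more in the test, not less.

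**The case against.** The case on the other side is substantial, and much of it stands.

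- A reader might infer that women are invited to groups at one set of units and to leaflets at the other. The article says only that recruiters give an information sheet and briefly describe the study. It does not say the sheet is arm-specific or that women know the arm before consent. An arm-neutral sheet may already exist in the full protocol.
- A reader might infer that the arm is disclosed before any woman is approached. That follows from the natural reading of the disclosure sentence but is not stated.
- It would be wrong to say that role separation is the only safeguard. The screening form, recorded exclusion reasons and recruitment comparisons are real, though they detect rather than prevent.
- Motivation is not unmeasured. Table 2 lists motivation, self-efficacy, self-regulation and social support at baseline, so imbalance in these scores can be seen and adjusted for.
- A full list of covariates is commonly left to an analysis plan, which is not shown. The article does not say baseline BMI is the only individual covariate. This is a fair limit on the covariate part of the point, but an analysis plan cannot conceal recruitment after the fact.
- Groups that begin at each woman's recruitment make later disclosure to units hard, and the article justifies the cluster design by contamination and group delivery.

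What remains is that unit staff can know the arm during enrolment, no section keeps it from women until baseline is complete, and the bias section does not address this.

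**Conclusion.** The point holds as a design weakness that should be fixed. As written, the plan leaves the arms open to differential enrolment that unit-level balancing and baseline BMI do not address. The bias is possible, not demonstrated.

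Its direction is uncertain. A reader might infer that it must flatter the intervention because motivated women would be drawn to the groups. Equally, women who join a control unit without groups could be the more self-motivated, which would bias towards no effect.

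The range of 0.19 to 0.48 kg/m² (13 to 32% of the target) rests entirely on the assumed imbalance, partial correlation and baseline correlation. A reader might push the upper end to 0.5 × 0.3 × 4.5 = 0.68 kg/m², or 45%. That treats the SD from the unadjusted sample size calculation as a residual SD, which would require baseline BMI to predict nothing about 12-month BMI.

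**What to change.** 1. Use the same arm-neutral information sheet and script at all 20 units. Tell each woman her unit's arm only after consent and all baseline measures are recorded. Keep women who then decline the groups in the intention-to-treat set. This removes selection by women's preference, but not selection by staff who know the arm. The cost is some non-uptake after disclosure, which dilutes the contrast, and ethics agreement to the wording. If such a sheet is already in use, the protocol should say so and state what women and recruiters know at consent.
2. Pre-specify a primary or key supporting model that adjusts for individual baseline variables: the Table 2 motivation and self-efficacy scores, age, parity, ethnicity, smoking, social class, weight-loss history and gestation at baseline. The article already names these as baseline measures or factors for exploratory analysis, and gestation is needed for eligibility, so the cost is analysis specification only.
3. Tabulate the proportions approached, excluded (with reasons) and consented by arm as well as by site, from the existing screening form. This needs no new data, and it is the main check on the staff-driven selection that item 1 leaves open.
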